### Secondary data

Secondary data analyses of EHR data and NYC Community Health Surveys data will provide additional context at the community, health system, and patient levels.

#### Data sources 

Secondary data for the needs assessment are from 2 main sources: (1) New York City Community Health Survey datasets and (2) NYU Health system Epic EHR. All secondary datasets will be obtained and managed by the study analyst. The full CHS 2018 and 2019 datasets will be downloaded under a data use agreement, approved by the NYC Department of Health and Mental Hygiene (DOHMH). The full datasets will be provided to the study analyst by an authorized NYC DOHMH representative. Patient-level Epic data from individual primary care practices will be acquired by the Clinical Research Data Management Core (DataCore) group at NYULH and provided to the study analyst. To ensure that patient confidentiality is maintained, the patient data will be de-identified and stored in a secure database. Only the study analyst and other pre-specified study team members will have access to identifying information.

#### Measures

##### 2018–2019 NYC community health survey measures

A descriptive analysis of 2018–2019 New York City CHS data will be used to characterize the outer setting in which PACE will operate. Measures explored in the datasets will include sociodemographic, behavioral, and relevant clinical variables, stratified by race, ethnicity, and HTN diagnosis. Sociodemographic variables will include health insurance status, age, sex, body mass index (BMI), marital status, parental status, number of adults in the household, education level, employment status, NYC borough, poverty level, perceived level of neighbors’ willingness to help fellow neighbors, and neighborhood poverty. Clinical variables will include whether respondents checked their BP in the last 30 days, HTN diagnosis, HTN medication(s) status, and whether participants were diagnosed with diabetes, obesity, or asthma. Behavioral variables will include smoking status, drinking status, fruit/vegetable consumption, sugar-sweetened beverage consumption, and physical activity status. Analysis of these variables will provide an overview of the population characteristics and comorbidity burden of the population to be engaged during PACE implementation.

##### NYU health system epic EHR (patient data)

A descriptive analysis of 2018–2021 NYULH EHR data, collected from the Epic platform, will help to characterize HTN burden and risk factors among patients within NYULH primary care practices. Measures explored in the datasets will include sociodemographic and clinical factors. Sociodemographic variables include race, health insurance status, age, sex, and NYC borough for current patients within NYULH practices. Clinical variables include medications (i.e.: HTN classes and dosages), medical comorbidity (i.e., diagnosis of diabetes, obesity, stroke, and/or chronic kidney disease), Charlson Comorbidity score, social history (i.e., smoking and drinking status), and patients’ clinic visit history. In addition, HTN diagnosis and BP readings (2018 to 2021) will be extracted from the EHR to categorize the patients in order to explore their HTN risk levels. Patients will be categorized into four groups: (1) HTN diagnosis with controlled BP; (2) HTN diagnosis with uncontrolled BP; (3) no HTN diagnosis and at least 2 uncontrolled BP readings (1 week apart); and (4) no HTN diagnosis and at least 2 elevated BP readings (1 week apart).

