**Electronic Health Record data**

To evaluate the 2018–2021 NYULH EHR data, baseline characteristics and outcomes will be summarized descriptively and graphically. Continuous variables will be summarized with means, standard deviation, medians, and ranges. Categorical variables will be analyzed with frequency distributions. We will group patients to create variables as follows: group 1 will contain patients with diagnosis of HTN and who have a controlled BP reading (systolic blood pressure [SBP] <130 and diastolic blood pressure [DBP] <80) based on mean of the last two BP readings; group 2 will contain patients with a diagnosis of HTN who have an uncontrolled BP reading (SBP≥130 or DBP ≥80) based on the mean of the last two BP readings; group 3 will contain patients without a diagnosis of HTN who have at least 2 uncontrolled BP readings; and group 4 will contain patients without a diagnosis of HTN who have at least 2 elevated BP readings (120≤SBP≤129 and DBP ≤ 80). To examine the associations between the variables, the chi-square test for categorical variables and the Kruskal-Wallis test for ordinal or interval variables will be used. *P*-values of these tests which are less than or equal to the specified significance level will be used to examine associations between variables. Two 2-way contingency tables will examine Race by all other variables and Group by all other variables. A three-way contingency table will be conducted to examine Hypertensive diagnosis and Race by all other variables. The table will examine proportions across the two main variables of interest (Hypertension diagnosis and Race). Lastly, we will conduct a multinomial logistic regression model for our nominal outcome variable, group, with *P*-values and odds ratios to examine the association between categories of groups.

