##### Triangulation and synthesis of findings

Triangulation will be used to integrate the multiple data sources, in order to improve the understanding of the context in which PACE will be implemented in primary care practices in NYC. We will use a concurrent triangulation approach [49] to examine instances of data congruence and or incongruence. This will also help to strengthen our interpretation and ensure that we have captured all potential participants at risk in the community (informed by the CHS data) and those already in the NYU healthcare system but undiagnosed and uncontrolled. The focus group and interview discussions will help to inform our understanding of the quantitative data and collaboratively work with the various stakeholders to identify facilitators to implementation and derive potential solutions to contextual challenges during PACE implementation. Following best practices for mixed methods research [50], we will construct a joint display [51] that integrates the data sources. Constructs to be integrated include community and neighborhood characteristics, patient-level determinants of HTN control, organizational capacity for change, availability of resources to support change, and attitudes toward EBIs. Should the data be divergent, we will assign higher credence to the qualitative data which offer richer explanation about participants’ attitudes and behaviors [50]. We will incorporate best practices in data visualization to transform these large bodies of disparate data into timely, digestible, and actionable insights that will inform the PF strategy.

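### The four EHR groups are not exhaustive: without undiagnosed normal-BP patients, the grouped analysis has no reference category and no full denominator for HTN burden and risk factors

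*Protocol article*

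**What the plan says.** The protocol article's section on NYU health system Epic EHR patient data describes a descriptive analysis of the HTN burden and risk factors of patients in the NYULH practices. It lists variables for current patients and then states: "Patients will be categorized into four groups".

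The Electronic Health Record data section under Data analyses defines them:

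- "group 1 will contain patients with diagnosis of HTN and who have a controlled BP reading", judged on the mean of the last two readings;
- "group 2 will contain patients with a diagnosis of HTN who have an uncontrolled BP reading", judged the same way;
- "group 3 will contain patients without a diagnosis of HTN who have at least 2 uncontrolled BP readings";
- "group 4 will contain patients without a diagnosis of HTN who have at least 2 elevated BP readings".

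That section cross-tabulates Group with all other variables. It adds "A three-way contingency table will be conducted to examine Hypertensive diagnosis and Race by all other variables", and finally "we will conduct a multinomial logistic regression model for our nominal outcome variable, group". No predictors are listed for the model.

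The Triangulation and synthesis of findings section says that the combined sources should capture "those already in the NYU healthcare system but undiagnosed and uncontrolled".

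**The concern.** A patient enters the grouped analysis with an HTN diagnosis, or without one but with two qualifying readings of the same kind. An undiagnosed patient with normal BP does neither. Nor does an undiagnosed patient with one uncontrolled and one elevated reading. Because group is the outcome of the multinomial model, these patients cannot contribute to it.

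Two things the stated aim needs are then missing. Burden is a proportion of all practice patients, and the four groups sum only to the patients who are diagnosed or have repeated raised readings. Risk factors call for a comparison with patients who do not have the condition, and no such group exists. The model can contrast controlled with uncontrolled, or diagnosed with undiagnosed raised BP. It cannot show who has HTN or raised BP rather than neither.

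The same gap affects the case-finding purpose in the triangulation section: group 3 cannot be expressed as a share of the undiagnosed.

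**Working it through.** The protocol gives no group sizes, odds ratios or power for this analysis, so there is no figure to reproduce. The check asks which quantities change when the ungrouped patients are left out.

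**Inputs**

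- Diagnosis rates from the Background: 43.5% of Black and 27.5% of White adults in NYC.
- Control rates from the Background: 48.5% and 55.7%, national.
- Shares of undiagnosed patients falling in groups 3 and 4: not in the protocol, so assumed. Main set: Black 25% and 15%, White 20% and 10%. Three other sets give the ranges below: (Black 20/15, White 20/15), (Black 30/20, White 15/10) and (Black 15/10, White 25/15).

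**1. Share of patients with a group** = diagnosed + undiagnosed × (group 3 share + group 4 share).

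- Black: 0.435 + 0.565 × 0.40 = 0.661
- White: 0.275 + 0.725 × 0.30 = 0.4925

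So 33.9% of Black and 50.75% of White patients would have no group.

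**2. Group proportions (these change).** Group 2 = diagnosed × (1 − control rate).

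- Black: 0.435 × 0.515 = 0.224 of all patients; 0.224 / 0.661 = 0.339 of grouped patients
- White: 0.275 × 0.443 = 0.122 of all patients; 0.122 / 0.4925 = 0.247 of grouped patients

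Over the four sets the grouped figure runs from 31.2% to 38.9% (Black) and from 21.6% to 26.7% (White), against fixed full-population values of 22.4% and 12.2%.

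**3. Group 3 as a share of the undiagnosed (this changes).** By assumption it is 25% (Black) and 20% (White). With only groups 3 and 4 available, the calculable share is 25/40 = 62.5% and 20/30 = 66.7%, which answers a different question.

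**4. Odds ratios among the four groups (these do not change).** For any two retained groups j and k, conditioning on being in groups 1–4 divides both P(j|x) and P(k|x) by the same quantity, so their ratio is unchanged. For group 2 vs 1, Black vs White: (0.515/0.485) / (0.443/0.557) = 1.335 with or without the ungrouped patients. Groups 3 and 4 vs 1 give 0.707 and 0.849 both ways.

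A multinomial model fitted to 200,000 simulated patients, with race and one covariate, agrees. The race odds ratios vs group 1 were 1.354, 1.221 and 1.095 with five categories, and 1.355, 1.220 and 1.094 after dropping the fifth (33% of patients).

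**5. Contrasts with the residual group (these cannot be estimated from four groups).** Group 2 vs residual, Black vs White:

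- residual: Black 0.565 × 0.60 = 0.339; White 0.725 × 0.70 = 0.5075
- odds ratio: (0.224/0.339) / (0.122/0.5075) = 2.75 from unrounded cells

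Over the four assumed sets it runs from 1.89 to 3.54.

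**The case against.** A reader might go further and infer that the omission distorts race odds ratios, for example by hiding a Black–White difference in diagnosis. The protocol does not support that.

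- Race is not named as a predictor in the EHR model. Even if it is one, odds ratios among the four groups are unaffected (step 4).
- A collapsed diagnosed-versus-undiagnosed odds ratio by race would be sensitive to the restriction, but the protocol plans one only for the Community Health Survey, which does not use these groups.
- The EHR race and diagnosis tables are not said to be limited to grouped patients.
- If they were, the illustrative value of 2.03 in all patients would become anything from 1.01 to 3.25 over the assumed shares, and would stay at 2.03 when the shares are equal by race. Neither direction nor size can be claimed.

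It can also be said that the EHR work is descriptive, that the main outcome is a facilitation strategy, that qualitative findings take priority, and that groups 3 and 4 suit case-finding. All of this stands and limits the consequence: no trial effect estimate depends on this model. Predictors and the reference category may properly be left to a fuller plan. The grouping itself is fixed in two places in the article, however, and neither limits the aim to at-risk patients.

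The triangulation argument is only secondary. The protocol plans a joint display of constructs, not a comparison of odds ratios between the survey and the EHR.

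**Conclusion.** The point holds in this limited form. The grouping is not exhaustive, and undiagnosed patients outside groups 3 and 4 drop out of the Group table and the multinomial model. The analysis can therefore compare diagnosed and repeatedly raised-BP patients only with one another, which falls short of its stated aim.

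The loss is one of missing contrasts and a missing denominator, not of bias in the contrasts that remain. The non-exhaustiveness follows from the definitions alone. The sizes shown are illustrative: they combine citywide diagnosis rates, national control rates and assumed shares, none of them specific to the NYULH practices. The change is worth making before the EHR analysis is run, but the validity of the later trial does not depend on it.

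**What to change.** - Add a fifth, residual group: no HTN diagnosis and not meeting group 3 or group 4, among patients with at least two BP readings. Defining it as a remainder, rather than as normal BP, also places patients with mixed or single raised readings. Describe it accordingly as patients without repeated raised readings.
- Use this group as the reference category in the multinomial model.
- Run the race and diagnosis tables on all patients with at least two readings, state each table's denominator, and report how many patients have fewer than two readings.
- If the restriction to four groups is intended, limit the stated aim to diagnosed or raised-BP patients and drop the reference to burden among practice patients generally.

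The cost is a few sentences and possibly a wider extract from the same EHR source. A fifth group makes the scheme exhaustive but not mutually exclusive. A patient with two uncontrolled and two elevated readings meets both group 3 and group 4, so a precedence rule should be stated in the same edit.

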##### Ethics and data storage protocol

The study protocol and activities were approved by the NYU Grossman School of Medicine Institutional Review Board on November 19, 2021. Informed consent will be obtained from all study participants. Quantitative data collected for the purposes of this study will be anonymized and stored in a secure database under the participant’s unique identifier. Identifying information will be available only to the study analyst and approved study staff. All transcribed qualitative data will be anonymized and stored in secure, password-protected files accessible only to study staff.

#### Main outcome

The primary outcome of this needs assessment is a context-specific tailored practice facilitation strategy to be implemented among 25 primary care practices and 2 pilot sites in NYC, in order to improve HTN control among Black patients.

### Data analyses

All statistical analyses will be conducted in R (R Foundation for Statistical Computing, Vienna, Austria) and qualitative analyses will be conducted in Dedoose qualitative analysis software. Findings from all data sources will be integrated and triangulated to generate themes, supplemented by quantitative findings. We will prioritize findings from the qualitative data, which by nature may provide more robust findings and richer understanding of the implementation context. The triangulation of these data sources will inform the PF strategy. Below, we describe in-depth the analyses for each data source.

#### Primary data

##### Primary data analyses

**Quantitative surveys conducted among health systems leadership, providers, and staff**

Quantitative analysis of the surveys will involve conducting descriptive and advanced statistical analyses; we will summarize continuous variables with means, standard deviations, medians, and ranges and will summarize categorical variables with frequency distributions. For continuous variables, we will display the distribution of response and will run ordered logistic regression. We will run chi-square tests for binomial categories. Descriptive analyses of the site and respondent characteristics will be conducted to characterize the implementation context. Site and respondent characteristics will be represented using descriptive statistics (mean, standard deviations, frequencies) to provide documentation and description of the practices, implementation components, and context. Findings will be compared across sites.

**Qualitative analysis**

Data from the interviews and focus groups sessions will be automatically transcribed in the WebEx platform (virtual sessions) or manually transcribed verbatim by study staff (in-person sessions). Analyses will be independently conducted in Dedoose qualitative analysis software platform by study team members. Analyses will follow an open thematic coding process, using a mix of inductive and deductive primary coding. An a priori codebook, which captures key study measures, will be developed, upon which coders will build in order to capture emerging codes. Throughout the analysis, coders will utilize practice member checking to make sure that we have adequately captured emerging themes and reflections. Qualitative sessions will be double coded by two coders, and inter-rater reliability will be evaluated. Coders will reconcile interviews until adequate reliability is achieved (Krippendorff’s alpha > .80). Should data reach saturation, qualitative sessions and analyses will be concluded.

#### Secondary data

##### Secondary data analysis

**CHS 2018–2019 data**

Using the CHS datasets, we will conduct descriptive statistical analyses to characterize the catchment population. We will summarize categorical variables (measures described above) and perform frequency distributions. Survey weights from 2018 to 2019 will be combined to estimate the population. Sociodemographic and behavioral variables will be stratified by the variables “Race,” “Ethnicity,” and “Hypertension Diagnosis” to explore the relationships between these variables. Two 2-way contingency tables will examine “Race” and “Hypertensive Diagnosis” by all other variables. Chi-square test for categorical variables and Kruskal-Wallis test for ordinal variables will be used to check the relationships between the variables. A three-way contingency table will be conducted to examine “Hypertensive Diagnosis” and “Race” by all other variables. The table will include proportions across the two main variables of interest (i.e., Hypertensive Diagnosis and Race). A logistic regression model will be conducted to examine the *P*-values for significance and to calculate odds ratios for “hypertensive diagnosis” as response variables by “Race” and other variables as predictor variables.

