### Primary data

#### Study settings and participants

##### Study settings

To assess context at multiple levels, the study activities will be carried out in a number of settings. The surveys, interviews, and focus groups will be implemented in primary care practices affiliated with NYULH (inner setting) and participating CBOs and FBOs (outer setting). Primary care practices identified as implementation sites are located in Brooklyn, Manhattan, Queens, and Greater Long Island. They contain a range of approximately 70–2400 eligible patients (i.e., Black patients with a HTN diagnosis and at least 1 uncontrolled BP reading over a 2-year period between 2018–2021).

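### The tests named for the weighted CHS data and for EHR patients grouped in practices carry no design-based or cluster adjustment; run as named, their p-values would generally be too small

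*Protocol article*

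**What the plan says.** All quotes are from the Protocol article.

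**CHS 2018–2019 data.** The stated purpose is descriptive: "we will conduct descriptive statistical analyses to characterize the catchment population". The weights are given one role: "Survey weights from 2018 to 2019 will be combined to estimate the population". The bivariate tests follow: "Chi-square test for categorical variables and Kruskal-Wallis test for ordinal variables will be used to check the relationships between the variables". A model with hypertension diagnosis as response comes last: "A logistic regression model will be conducted to examine the *P*-values for significance and to calculate odds ratios". The section does not say whether weights or sampling design enter the tests, the model or their standard errors.

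**Electronic Health Record data.** For associations, "the chi-square test for categorical variables and the Kruskal-Wallis test for ordinal or interval variables will be used". A p-value at or below a specified level is the criterion, but no level is given. For the four blood-pressure groups, "we will conduct a multinomial logistic regression model for our nominal outcome variable, group, with *P*-values and odds ratios". No practice effect or clustered standard error is mentioned.

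**Data structure.** Under Data sources: "Patient-level Epic data from individual primary care practices will be acquired". On the implementation practices, Study settings says "They contain a range of approximately 70–2400 eligible patients".

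**The concern.** In their standard form, the chi-square test, the Kruskal-Wallis test and both logistic models assume independent, equally weighted observations. Neither dataset fits that description.

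- **CHS.** An unweighted test refers to the respondents, not to the population that the weighted tables describe. A weighted test with an independence-based variance ignores the precision lost to unequal weights. If population-scaled weights are read as counts, the test behaves as if the whole population had been interviewed. The standard Kruskal-Wallis test takes no sampling weights at all.
- **EHR.** If both the blood-pressure group and a covariate vary by practice, patients in one practice do not supply independent information about their association. A naive p-value is then too small.

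At stake is which associations go forward as findings. Community characteristics and patient-level determinants of control enter the joint display described under Triangulation and synthesis of findings, and that display informs the facilitation strategy.

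**Working it through.** The article states no sample size, significance level, ICC or design effect for these analyses, so there is no figure to reproduce. What follows is illustrative. Two-sided alpha of 0.05 and all CVs and ICCs are assumptions.

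**Formula for both datasets.** If the true variance is DEFF times the naive variance, the actual error of a nominal 5% test is 2 × [1 − Φ(1.96/√DEFF)].

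**CHS.** Kish approximation, DEFF = 1 + CV² of the weights. This is the case of weights scaled to the sample size but with an independence-based variance; other features of the sampling design are left out.

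| Weight CV (assumed) | DEFF | True SE / naive SE | Actual error |
|---|---|---|---|
| 0.3 | 1.09 | 1.04 | 6% |
| 0.5 | 1.25 | 1.12 | 8% |
| 1.0 | 2.00 | 1.41 | 17% |
| 1.2 | 2.44 | 1.56 | 21% |

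**Pooling two years.** Suppose each year's weights sum to that year's population. Stacking them unscaled then gives totals about twice too large. A constant multiplier cancels from proportions and odds ratios, so only totals would be affected.

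**EHR, by formula.** For a patient-level covariate, DEFF = 1 + (m − 1) × ICC of outcome × ICC of covariate, with m patients per practice. The values 70 and 2400 are the ends of the range in Study settings; 500 is an assumed middle value.

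| m | ICC outcome | ICC covariate | DEFF | Actual error |
|---|---|---|---|---|
| 70 | 0.01 | 0.05 | 1 + 69 × 0.0005 = 1.03 | 5.4% |
| 500 | 0.01 | 0.20 | 1 + 499 × 0.002 = 2.00 | 17% |
| 2400 | 0.05 | 0.20 | 1 + 2399 × 0.01 = 24.99 | 70% |
| any | any | 0 | 1.00 | 5% |

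**EHR, by simulation.** 27 practices with log-spaced sizes from 70 to 2400 (18,401 patients in all), outcome prevalence 45%, covariate prevalence 30%, practice-level rates of the two drawn independently, no association within practices, 1000 runs. Rejection rate of the pooled chi-square test at 5%:

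| ICC outcome | ICC covariate 0 | 0.05 | 0.20 |
|---|---|---|---|
| 0 | 5.2% | 5.6% | 5.2% |
| 0.01 | 5.1% | 11.1% | 27.0% |
| 0.02 | 6.1% | 18.0% | 42.3% |
| 0.05 | 5.8% | 27.9% | 58.7% |

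The error stays near 5% when either ICC is zero and rises steeply when neither is.

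**Limits of these inputs.** The 70–2400 range counts only Black patients with hypertension and at least one uncontrolled reading. The EHR analysis also covers other races and undiagnosed patients. The count of 27 describes the program; the EHR sections do not say how many practices supply the data.

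**The case against.** The strongest reply is that the article is silent, not wrong. It never says that weights or clustering are ignored. The weights appear in the same paragraph as the tests, and R runs adjusted versions of all of them. A condensed article may leave the variance estimator to a fuller plan. The analyses are also descriptive: the main outcome is a facilitation strategy, qualitative findings take priority, and they prevail where the sources diverge.

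Much of this stands, and it rules out several stronger readings that a reader might infer:

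- *The standard errors and p-values are wrong.* That would treat silence as a decision to ignore weights and practice. The bias also depends on weight variation and on two ICCs, none of which is reported.
- *EHR design effects are about 7 to 31.* With an assumed 600 patients per practice, 1 + 599 × 0.01 = 6.99 and 1 + 599 × 0.05 = 30.95. That formula is for a covariate constant within a practice, whereas the EHR measures listed are patient-level.
- *The pooled CHS population is doubled.* This holds only if the weights are stacked unscaled, which combining them does not imply.
- *Race is confounded with practice.* This is plausible for sites across several boroughs and Long Island, but no racial mix by practice is reported. A system-wide race contrast is a legitimate descriptive target.

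What does not stand is that brevity settles the matter. The article goes down to named tests, table dimensions, blood-pressure cut-points and the weighting step. It makes p-values the criterion for association, and one of its named tests cannot use the weights in standard form.

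**Conclusion.** The point holds in a limited form. The article fixes tests whose standard versions do not suit weighted survey data or patients grouped in practices, and it names no adjusted version. Run as named, the CHS tests would not correspond to the weighted estimates. P-values would be too small when weights are used with an independence-based variance, and in the EHR when outcome and covariate both cluster by practice.

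Under the assumptions shown, a nominal 5% test has about 6% to 21% error in CHS. In the EHR it ranges from about 5% to 59% in the simulation, and up to 70% by formula if every practice had 2400 patients. These are ranges over assumed inputs, not estimates for this study.

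Importance is minor to moderate. No primary hypothesis test or sample size rests on these results, but they do feed the strategy.

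**What to change.** **CHS.** State that the weights are rescaled when the two years are pooled, for example by halving each year's weights, so that totals refer to an average year. Use survey-design methods throughout: Rao-Scott chi-square, a design-based rank test in place of the standard Kruskal-Wallis test, and survey-weighted logistic regression.

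**EHR.** Use practice-clustered standard errors in the multinomial model, with a small-cluster correction if the number of practices is near 27. Use cluster-adjusted bivariate tests. Report odds ratios with confidence intervals. A model with practice effects, giving within-practice race odds ratios, may be added beside the system-wide contrast but should not replace it.

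**Cost.** Some added R code and a few sentences of text; no new data. The price is wider confidence intervals and probably fewer associations declared significant.
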